### Teachers’ training program and implementation phase with students

The intervention will consist of two phases for the experimental group: (1) a face-to-face teacher training phase, which includes two group sessions, one group booster session, and two individual follow-up sessions, and (2) an implementation phase, during which teachers will apply the strategies with their students (see Figure 1).

#### Teacher training program

Experimental PE teachers will participate in a training program designed to help them provide relatedness-supportive and class cohesion strategies while avoiding relatedness-thwarting behaviors. The training will be delivered by three experienced researchers in designing and implementing motivational teacher development programs, ensuring a close trainer-to-teacher ratio (~3 trainers per 4–5 teachers) to support implementation quality and fidelity.

##### Face-to-face teacher training phase

The training will be structured into two main parts (see Figure 1) and following the three-phase framework proposed by Reeve et al. (2022): (1) *Get Ready to Work*: theoretical foundations and awareness-building, (2) *How To?*: practical strategy development, and (3) *Peer-to-Peer Group Discussion*: collaborative reflection after implementation. This structure was selected for its evidence-based support in promoting long-term teacher behavior change and alignment with the intervention’s goals.

The first part, which will be conducted in late September, involves two group sessions, each lasting 3 h, that addressed the first two phases (i.e., [1] Get Ready to Work, and [2] How To?). After completing this phase, a round of classroom observations will be conducted to assess the implementation of the proposed strategies. The second part, a booster session, which will be delivered in January, focuses on the third phase (i.e., [3] Peer-to-Peer Group Discussion). This session will be informed by the first observations and teachers’ weekly logs and will be followed by a second round of observations to support teachers’ development and practice integration further. Following this structure, the training sessions will include several activities aimed at enhancing teachers’ theoretical understanding, co-creation of strategies, and practical application, as detailed below.

##### First group session

The first group session will address the initial phases of the training (i.e., [1] Get Ready to Work, and [2] How To?), focusing on strengthening teacher relationships, introducing the study’s aims, and familiarizing teachers with the theoretical frameworks underpinning the intervention (i.e., SDT and CMC). First, teachers will report their prior knowledge and experiences with relatedness-supportive and class cohesion strategies, and then complete the questionnaires on the study variables (T1). To introduce theoretical frameworks, teachers will then reflect individually, using color-coded post-its to sort their relatedness-support and class-cohesion strategies into three groups: yellow for consistently used, blue for occasional use, and pink for desired but not yet applied. Subsequently, teacher motivational behaviors (TMBs) related to relatedness-supportive and relatedness-thwarting (Ahmadi et al., 2023, see Supplementary Table 1) and guidelines for promoting task and social cohesion (Leo et al., 2023d, see Supplementary Table 2) will be presented. Teachers’ identified strategies will then be mapped onto these frameworks to facilitate their integration into practical instruction. The session will conclude with a discussion on the benefits of adopting relatedness-supportive practices and class cohesion strategies, followed by assigning a complementary reading to deepen participants’ theoretical understanding before the second training session (Leo et al., 2023d).

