## Abstract

Grounded in Self-Determination Theory and the Conceptual Model of Cohesion, relatedness satisfaction and class cohesion have been positively linked to learning-related outcomes. However, the benefits for both teachers and students of a training program focused on improving Physical Education (PE) teachers’ relatedness-supportive behaviors and class cohesion have not yet been explored. This study presents the protocol for a training program designed to provide PE teachers with relatedness-supportive and class cohesion strategies, as well as to avoid relatedness-thwarting strategies. Consequently, this program aims to enhance teachers’ interpersonal style and students’ motivational and (mal)adaptive outcomes in PE lessons. A randomized controlled trial with a mixed-methods approach will be conducted as part of a three-wave longitudinal study. Between 8–10 secondary PE teachers and their students will be assigned to either the experimental group or the control group. The face-to-face training program implemented with experimental group’s teachers will consist of two group sessions, one group booster session, and two individual follow-up sessions. After completing the training, teachers will implement the strategies over approximately six months during their PE classes. Beliefs, feasibility, and intention to apply the strategies, relatedness-supportive behaviors, relationship satisfaction with students, class cohesion, motivational variables, and (mal)adaptive outcomes will be assessed in PE teachers and their students at three distinct time points: before the training program (Time 1), at the end of the implementation (Time 2), and 2 months later (Time 3). Additionally, a focus group involving all experimental PE teachers will be held at the end of the implementation (T2). The results of this study will help determine whether this type of training program can benefit both students and teachers.

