## Method

### Context and design

The TRI-PE project is a randomized controlled trial (RCT) to be conducted in secondary schools within the region of Extremadura. In this region, the academic calendar extends over three terms, from early September to mid-June, with holiday breaks in December–January for Christmas and in March or April for Easter. Specifically, PE is mandatory for all secondary students who attend two coeducational 50-min weekly classes. As illustrated in Figure 1, the intervention will last 10 months, with assessments conducted at three time points: (1) baseline measurement at the end of the first month of the school year (first term, end of September; T1) to ensure that students have had several weeks to a fine-grained picture of the variables under investigation; (2) post-implementation assessment (second term, April; T2); and (3) 2-month follow-up post-implementation at the end of the academic year (third term, June; T3). This study has been approved by the Ethics Committee of University of Extremadura [114/2023] and complies with the principles of the Declaration of Helsinki.

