Teachers must meet the following inclusion criteria to participate in this study: (1) be an in-service PE teacher at the same school for the entire academic year; (2) complete the study questionnaires at three different time points; (3) not participate during the entire academic year in other intervention or training programs similar to this study; (4) attend all the training program sessions; (5) allow research team visits for classroom observation; and (6) participate in a focus group at the end of the intervention. Each PE teacher will recruit at least four classroom groups of no fewer than 16 students each, ensuring that at least 80% of the students in each group participate. Eligible students will be those aged 12–18 years from secondary schools. Participation will be completely voluntary and anonymous. School principals and students’ families will also be informed about the study’s aims and characteristics to obtain their informed consent for participation. The 80% participation rate applies only to baseline (T1); teachers not reaching it may be excluded, with replacements drawn from a waiting list. Dropout over time will not lead to exclusion if at least 60% of students complete all data points. The research team will make every effort to retain the full sample and minimize attrition throughout the study. Finally, the inclusion criteria for students’ participation in the intervention program will be: (1) obtaining consent from both parents/legal guardians and students; (2) commitment to completing the questionnaires assessing the study variables three times; and (3) regular participation in PE lessons.

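### Experimental teachers complete their T1 questionnaire inside the first training session, after allocation, and teachers replaced after the T1 participation check have no stated allocation rule

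*Protocol article*

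**What the plan says.** The Abstract defines T1 for teachers and students as "before the training program (Time 1". Context and design gives the date: "baseline measurement at the end of the first month of the school year (first term, end of September; T1". The training section gives nearly the same date for the sessions: "The first part, which will be conducted in late September, involves two group sessions".

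Under First group session, the experimental teachers first report their existing knowledge and experience of the target strategies and "then complete the questionnaires on the study variables (T1". The section on control teachers and students limits the control arm to filling in questionnaires at the same time points. The Blinding section says that teachers know their arm.

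Sample recruitment requires 80% student participation at T1 and adds: "teachers not reaching it may be excluded, with replacements drawn from a waiting list". The same section names a digital tool for randomisation but does not say whether it is used before or after that check.

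**The concern.** Hypothesis 4 compares the arms on what teachers report about themselves: beliefs, feasibility, intention, supportive behaviour and relationship satisfaction. These are subjective ratings by unblinded people. If one arm gives its baseline ratings in the training room, just after being asked about the strategies under study, and the other does not, the two baselines are not measured alike. The planned analysis would read any resulting gap as part of the intervention effect.

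The replacement rule raises a different problem. With 8–10 teachers, the comparison rests on the random allocation of very few units. A teacher who fills a vacated place was not allocated by chance, and the word *may* leaves exclusion to judgement, possibly with the arm known.

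**Working it through.** The plan gives no figure on this point, so there is none to reproduce. The check is mainly one of sequence, with short arithmetic for the consequences.

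**Sequence for teachers**

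1. Teacher training program: "Experimental PE teachers will participate in a training program designed to help them provide relatedness-supportive and class cohesion strategies". Only that arm is trained, so allocation must come before session 1.
2. First group session, in order: report of existing knowledge and experience; T1 questionnaire; then "To introduce theoretical frameworks, teachers will then reflect individually, using color-coded post-its"; then the teaching behaviours, the cohesion guidelines and a discussion of benefits. The session also introduces the study's aims, at a point not given.
3. Control group teachers: the same time points, no session.

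So teacher T1 in the experimental arm comes after allocation, with the arm known and after a step that controls do not take. It does come before the framework content. The Abstract's definition can be met only in that narrow sense, because the questionnaire is itself a step of the first training session.

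**Effect on the contrast**

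Let δ be the true between-arm difference in mean change from T1 to T2, and s the shift in the experimental arm's mean T1 score caused by the setting.

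- Experimental change observed: (true change) − s
- Control change observed: (true change)
- Difference observed: δ − s

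The bias is −s, with a coefficient of 1. The same holds for T1 to T3; T2 to T3 is unaffected. As an illustration only, an assumed upward shift of 0.1 to 0.3 SD lowers the contrast by 0.1 to 0.3 SD, and a downward shift raises it by as much. The planned teacher covariates (age, sex, experience, school type and location) do not carry s and cannot remove it.

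**Replacement**

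- Inputs: 8–10 teachers, split equally, so 4–5 per arm; and "Each PE teacher will recruit at least four classroom groups of no fewer than 16 students each".
- Share of an arm per replaced teacher: 1/5 = 20% to 1/4 = 25%.
- Share of all teachers: 1/10 = 10% to 1/8 = 12.5%.
- Students in that teacher's classes: at least 4 × 16 = 64.

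The article gives no failure rate for the 80% check. If each teacher fails independently with probability q and every failure leads to replacement (assumptions), the chance of at least one replacement among m teachers is 1 − (1 − q)^m:

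| q | m = 8 | m = 10 |
|---|---|---|
| 5% | 34% | 40% |
| 10% | 57% | 65% |
| 20% | 83% | 89% |

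**Order of check and randomisation**

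Two orders fit the text. If student T1, the check and any replacement all precede randomisation, nothing is lost. If the check follows randomisation, a replacement who takes the vacated place is not randomised. In the experimental arm that teacher may also have missed session 1, which conflicts with the inclusion criterion of attending every session. T1 and both sessions fall in late September, and the text does not say which order applies.

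**The case against.** A reader might infer that T1 is no true baseline for the whole trial and that randomisation is broken. The article does not support either statement.

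On the baseline, the Abstract puts student T1 before training, and implementation with students starts in October. Students do not know their teacher's arm, data collectors have no allocation list, and teachers are out of the room when students answer. Even if a session came a few days before student T1, planned delivery to students would not have begun. The in-session problem therefore concerns teacher self-reports, not the student outcomes of Hypotheses 1–3. For teachers too, the post-it reflection and the framework content follow the questionnaire; only a short self-report precedes it.

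On randomisation, its timing against the 80% check is not given and exclusion is discretionary, so a breach is possible but not established. Figure 1, the timeline, could not be consulted and may settle the order. A further worry, that classes could be chosen after teachers learn their arm, rests only on silence in a condensed article and is not pressed.

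These points limit the scope. They do not change the fact that experimental teachers' T1 is placed after allocation in a session that controls do not attend, or that a replacement rule tied to T1 comes without an allocation rule.

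**Conclusion.** The concern holds in two limited parts.

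First, teacher T1 is collected after allocation and under different conditions by arm. Any shift enters the Hypothesis 4 Time × Condition contrast in full. Neither its size nor its sign can be derived: an upward shift at T1 would understate a benefit and a downward shift would overstate it. The finding rests on the stated order of events in the first session and on training being confined to the experimental arm.

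Second, replacement after the T1 check has no stated allocation rule. If it occurs after randomisation, each replacement makes 20–25% of one arm non-randomised, together with all of that teacher's classes. This part is conditional on that order and on a replacement happening at all.

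Neither problem can be repaired in the analysis once the September data are in, so both should be settled before recruitment closes.

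**What to change.** - Take the T1 questionnaire out of session 1. Give it to teachers in both arms in the same way, with no preceding questions about the target strategies, before allocation is disclosed.
- State the order: teacher T1, student T1, 80% check and any waiting-list replacement, then randomisation, then session 1.
- Allow no replacement after randomisation.
- Bring the Abstract, Sample recruitment and First group session sections into line with this order.

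No extra measures are needed. The cost is scheduling. T1 was deliberately set at the end of September so that students have had several weeks of class, and implementation starts in October. T1 would have to move slightly earlier or session 1 slightly later, and the check, any replacement and randomisation must fit between them.

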##### Second group session

In the second group session, as part of Phase 2: “How To?,” teachers—drawing on the theoretical frameworks, TMBs, and the assigned reading—will continue to co-create practical strategies that reinforce students’ sense of belonging and class cohesion (i.e., task and social cohesion). In the last part of the sessions, strategies will be evaluated for feasibility, refined by consensus, and integrated into teaching plans for subsequent implementation.

##### Group booster session

Approximately 3 months after the start of the implementation, teachers will participate in a booster session aligned with Phase 3 (i.e., [3] Peer-to-Peer Group Discussion). This timing is designed to allow teachers sufficient opportunity to apply, experiment with, and refine the intervention strategies in real classroom settings. According to Reeve et al. (2022), teachers require a minimum of 1 month of practical experience to integrate new techniques effectively, engaging in processes of experimentation, trial-and-error, reflection, discussion, and collaborative problem-solving. The booster session will address implementation barriers based on teachers’ weekly logs and the first follow-up observation. Teachers will collaboratively explore solutions and engage in simulated PE teaching scenarios (i.e., video recordings of real PE lessons) to reinforce the application of relatedness-supportive and class cohesion strategies.

##### Individual follow-up sessions

In addition to group sessions, two individual follow-up sessions (before and after the booster) will be held between each teacher and a member of the research team. These one-on-one meetings will serve to personalize support, address context-specific issues, and offer tailored feedback based on classroom observations. During each follow-up session, the research team will use a structured protocol to assess the implementation of relatedness-supportive behaviors and class-cohesion strategies. After each observation cycle, an individualized report will be generated for each teacher, providing a detailed analysis of their instructional practices regarding the intervention aims. Specifically, the report will include: (1) an overview of the strategies effectively employed during the two observed lessons; (2) a set of additional relatedness-supportive and class cohesion strategies that could have been implemented to further enhance students’ sense of belonging, peer interactions, and class cohesion; and (3) tailored recommendations for future application and refinement of these strategies. These reports are intended as formative tools to help teachers reflect critically on their practice, identify areas for growth, and adjust instruction in alignment with the intervention framework.

#### PE implementation for experimental group students

The implementation phase will last approximately 6 months, from October to the end of March, as we plan to conduct a post-intervention follow-up measure in the final month of the academic year (i.e., June; see Figure 1). During this period, the co-created strategies will be implemented by the experimental group teachers. Relatedness-supportive and class cohesion strategies learned during the training program will be encouraged for implementation in the different teaching units of their annual teaching plan. Efforts will be made to ensure that teachers implement them as much as possible, in terms of variety, frequency, and intensity, in each PE class. The experimental group teachers will implement a common set of strategies; however, teachers will have the flexibility to adapt these strategies to their specific educational context, considering the characteristics and needs of their students. This process will be conducted under the supervision of a research team member.

#### Control group teachers and students

Teachers in the control group will not initially receive the training program and, consequently, will not intentionally implement any strategies aimed at supporting relatedness and class cohesion with their students. Their participation will only involve completing the questionnaires at the same time points as the experimental group teachers and students (see Figure 1). However, after the final assessment of the study, control group teachers will be invited to receive the same training program, enabling them to implement these strategies in the following academic year. A final report will also be prepared, outlining each teacher’s profile based on the teachers’ self-reports and their students’ perceptions. The training offered to control group teachers after the study will be identical in structure and content but will not involve additional data collection, as it is intended solely to offer equitable access to professional development opportunities.

#### Fidelity of the training program and intervention implementation

Firstly, an external researcher with expertise in SDT-based program design will attend every training session to assess compliance with the prescribed structure and strategies (i.e., congruent style). In addition, he will provide external feedback to the research team members implementing the program.

Secondly, the fidelity of the intervention will be examined in two ways. On the one hand, teachers will submit a weekly checklist via Google Forms, specifying which relatedness-supportive or -thwarting strategies and class-cohesion techniques they have implemented. This will allow teachers and researchers to be aware of the degree of implementation of the various strategies. On the other hand, an observer with experience in identifying TMBs in PE classes will observe two random classes from each PE teacher to assess the degree of implementation of the strategies. For this purpose, three different checklists will be used: (1) the same verification checklist that teachers complete weekly, which includes the co-created strategies developed during the training phase; (2) a checklist based on the TMBs for supporting and thwarting relatedness proposed by Ahmadi et al. (2023; see Supplementary Table 1); and (3) a checklist derived from the guidelines for promoting class cohesion developed by Leo et al. (2023d; see Supplementary Table 2). This multi-instrument approach will provide a more comprehensive assessment of fidelity and ensure the evaluation is aligned with both theoretical constructs and contextualized pedagogical practices.

### Measures

Various assessment instruments will be administered to all study participants at three different time points (September [T1], April [T2], and June [T3]; see Figure 1). During the administration of the students’ questionnaires, at least one research team member will be present in the classroom to address any questions or concerns, and teachers will be absent. Students will be informed that their responses are anonymous, and that neither teachers nor school staff will have access to individual data. The paper-based questionnaire will take approximately 15 min for both students and teachers to complete at each time point.

